## Abstract

**Background:**

Despite increases in HIV testing, only a fraction of people newly diagnosed with HIV infection enter the care system and initiate antiretroviral therapy (ART) in South Africa. We report on the design and initial enrollment of a randomized trial of a health system navigator intervention to improve linkage to HIV care and TB treatment completion in Durban, South Africa.

**Methods/Design:**

We employed a multi-site randomized controlled trial design. Patients at 4 outpatient sites were enrolled prior to HIV testing. For all HIV-infected participants, routine TB screening with sputum for mycobacterial smear and culture were collected. HIV-infected participants were randomized to receive the health system navigator intervention or usual care. Participants in the navigator arm underwent a baseline interview using a strengths-based case management approach to assist in identifying barriers to entering care and devising solutions to best cope with perceived barriers. Over 4 months, participants in the navigator arm received scheduled phone and text messages. The primary outcome of the study is linkage and retention in care, assessed 9 months after enrollment. For ART-eligible participants without TB, the primary outcome is 3 months on ART as documented in the medical record; participants co-infected with TB are also eligible to meet the primary outcome of completion of 6 months of TB treatment, as documented by the TB clinic. Secondary outcomes include mortality, receipt of CD4 count and TB test results, and repeat CD4 counts for those not ART-eligible at baseline. We hypothesize that a health system navigator can help identify and positively affect modifiable patient factors, including self-efficacy and social support, that in turn can improve linkage to and retention in HIV and TB care.

**Discussion:**

We are currently evaluating the clinical impact of a novel health system navigator intervention to promote entry to and retention in HIV and TB care for people newly diagnosed with HIV. The details of this study protocol will inform clinicians, investigators, and policy makers of strategies to best support HIV-infected patients in resource-limited settings.

**Trial registration:**

Clinicaltrials.gov. unique identifier:
NCT01188941.

## Background

The dual epidemics of HIV and TB remain a leading health care challenge in South Africa
[1,2]. Despite rapid expansion in the availability of antiretroviral therapy (ART), only about half of HIV-infected individuals are in care
[3]. The period following HIV diagnosis but prior to ART initiation represents a time of very high mortality, attributable in part to late TB diagnosis and poor rates of TB treatment completion
[2,4-6]; TB remains the leading cause of death among HIV-infected individuals
[7]. Interventions focused on integrating intensive TB screening into HIV diagnostic services and improving linkage to HIV and TB care would be of substantial benefit in controlling these epidemics.

Previous studies have shown that the paucity of symptoms, transportation barriers, stigma, and lack of self-efficacy and social support are all factors that negatively affect the likelihood of entering and remaining in HIV care
[8,9]. While most interventions have focused on retaining patients in care or improving ART adherence
[10-14], few studies have addressed the multiple barriers faced by HIV-infected individuals before entering care. A randomized controlled trial of a brief case manager intervention in the US improved linkage and retention in care at 12 months
[15,16]. However, no randomized studies of case managers or navigators to improve linkage to HIV care have been reported from resource-limited settings with high HIV and TB prevalence.

This paper describes the rationale and the design of a randomized controlled trial that aims to establish the efficacy of an in-person and mobile phone-based health system navigator (HSN) intervention in improving linkage to HIV and TB care among newly diagnosed HIV-infected outpatients in Durban, South Africa, and to evaluate the cost and cost-effectiveness of this intervention. We hypothesize that the HSN intervention will improve linkage to and retention in care for these diseases and lead to higher rates of ART initiation and TB treatment completion compared to the standard of care.

## Methods

### Study rationale

The design of this study is grounded in the Andersen model of health services utilization, which identifies environmental and patient characteristics that influence health-seeking behaviors
[17,18]. Andersen recognizes predisposing factors (i.e. demographic characteristics), enabling factors (factors that represent the actual ability to obtain care), and perceived needs (symptoms, values, and knowledge about health and the health care system), which together determine an individual’s use of the health care system
[17,18]. The goal of the trial is to evaluate the efficacy of a strengths-based case management approach, implemented by HSNs, for effecting modifiable patient factors that will improve linkage to HIV and TB care
[19].

### Study design

The study is a multi-site randomized controlled trial, known locally as the Sizanani (Zulu for “Help Each Other”) Trial. Participants were enrolled at four sites in the greater Durban area. These sites comprised two hospital-affiliated outpatient departments and two municipal clinics (e.g. nurse-driven primary health care sites). All patients were enrolled in the study and randomized prior to HIV testing to reduce differential acceptance rates by results of HIV testing. Participants were tested for HIV and all newly-identified HIV-infected participants received TB screening. HIV-infected participants were either in the intervention group, and were assigned to a HSN, or the control group, the current usual care in Durban (Figure 
1). Nine months following enrollment, medical records will be reviewed, and all participants will be contacted by telephone to assess linkage to HIV care and TB treatment completion. Follow-up for the study is ongoing.

**Figure 1 F1:**
[figure not shown]
**Consort diagram of the study design.** OPD: outpatient department.

### Randomization

After completing the baseline questionnaire, enrolled participants were randomized, prior to HIV testing, to the intervention or the usual care arm. Randomization was stratified by site and gender, with blocks of varying length. Randomization assignments were created by the Boston-based Data Coordinating Center. A randomization table that was inaccessible to the South African research assistants was embedded in a Handheld Assisted Patient Interview (HAPI) device and provided randomization assignments for consecutive study numbers.

### Setting and participants

Participants were enrolled at four outpatient sites in KwaZulu-Natal. McCord Hospital predominantly serves an urban population in the greater Durban area. McCord was part of the PEPfAR-funded scale-up of ART from 2004 to 2012. St Mary’s Hospital is a state-aided district hospital, serving a peri-urban population, which began offering PEPfAR-funded ART starting in 2003. In addition, participants were enrolled in two primary health municipal clinics: Mariannridge and Tshelimnyama. In August 2012, the McCord enrollment site closed; enrollment continued at the other three sites. All adults (≥18 years old), English- or Zulu-speaking were eligible if they met the following criteria: presenting Monday through Friday for outpatient care, voluntarily had an HIV test, were able and willing to give informed consent, reported no prior positive HIV test, were willing to share HIV and TB test results with research staff, and were not known to be pregnant at the time of screening.

### Enrollment procedures

Eligible participants signed a consent form (in English or in Zulu) in a private area, and the research assistant then administered a baseline questionnaire comprised of detailed demographic information, as well as clinical information including depression, social supports and self-identified barriers to engaging in care. At enrollment, participants also provided contact details, as well as the contact information for a family member or friend who could be telephoned if the participant could not be reached. Participants were asked their preference for Zulu or English SMS text. Participants then underwent counseling and rapid HIV testing by the study sites’ HIV counseling staff as per standard South African protocol
[20] and received test results immediately. All HIV-infected participants were counseled regarding the meaning of the HIV test result, the appropriate next steps, and how to obtain HIV treatment if needed; they were offered venipuncture for a CD4 count, and instructed to return for results approximately two weeks later. HIV-infected participants were then seen by a Sizanani nurse who administered a brief standardized TB symptom questionnaire and obtained history related to prior and current TB treatment. Participants expectorated a single sputum specimen, spontaneously or using nebulized 3% hypertonic saline, if needed. Sputum specimens were transported daily to the TB laboratory of the University of KwaZulu-Natal. All sputum samples were stained to assess for acid fast bacillus (AFB) smear, and were processed for *Mycobacterium tuberculosis* culture with drug susceptibility testing. The TB nurse contacted participants upon receipt of a positive AFB or culture, and they were directed to the site TB nurse for registration and TB treatment initiation.

### Health System Navigator (HSN) intervention

The HSN provided focused personalized support to patients in the period immediately following HIV diagnosis, with or without an accompanying TB diagnosis, to improve linkage to care. The HSN sought to identify and influence modifiable patient factors, including self-efficacy and social support, through a strengths-based case management approach
[19,21]. The HSN conducted a brief strengths-based interview to help patients identify their own assets to overcome barriers to obtaining care. They were also provided with lists of local HIV and TB care facilities to assist participants with identifying a convenient and acceptable care site if the participant did not want to receive care at the study site. The HSNs provided their study mobile phone number to participants, and were available to respond to questions. Lastly, the HSNs physically showed participants the location where blood could be taken for a CD4 count, as well as the location of the HIV clinic. Participants then continued with their routine care at the study site. Once the patient left the clinic, the HSN contacted the subject through regularly scheduled SMS reminders to retrieve test results and keep appointments, as well as providing psychosocial support through regular telephone calls (Table 
1). During each telephone contact, the HSN assessed where participants are on the HIV and TB care pathway (Figure 
2). The HSN downloaded weekly reports from the study database which contains lists of patients due for SMS and telephone calls. Each SMS was delivered in the subject’s preferred language and did not mention the study site, HIV or TB. The content of the SMS was standardized, but the message was dictated by the subject’s position in the care pathway. For example, if blood for a CD4 count had been taken, but the subject had not yet picked up the results, the SMS read “Sizanani: please pick up results in the next week.” All patient contacts and the time required for attempted patient contacts were logged daily by the HSN to allow for an assessment of the personnel time required to perform the intervention.

**Table 1 T1:** Health System Navigator (HSN) phone call and SMS schedule

**Week Number Post-Enrollment**									
		**1**	**1.5**	**3**	**4**	**6**	**8**	**12**	**16**
**Type of Contact***	**SMS**		X	X		X		X	
	**Phone**	X			X^†^		X	X	X‡

^*^If participants are not reached at the time of a telephone call, the contact schedule is intensified by turning the next designated SMS reminder into a phone call. For example, if a subject is not reached at the week 1 phone call, the week 1.5 SMS becomes a phone call. The contact schedule differs slightly by study site, based on the site-specific time to return for CD4 count results.

^†^HSN calls subject’s alternative contacts if the subject is still unreachable.

^‡^ Participants are considered unreachable if the HSN still cannot contact them.

**Figure 2 F2:**
[figure not shown]
**HIV and TB care pathways.** ART: Antiretroviral therapy; TB: tuberculosis.

### Usual care

Patients randomized to the usual care arm were given a date and time to return two weeks later to receive their CD4 count results from the HIV counselors. As in the intervention arm, patients with a positive HIV test were redirected to the TB focal point at each site. A trained study nurse administered a brief questionnaire regarding TB symptoms and collects a sputum specimen. Patients then proceeded to the clinician, where they resumed their usual care. The participants in the usual care arm had no further contact with the study staff until the 9-month follow-up phone call.

### Research personnel training

The study staff included a project manager, one enrolling research assistant at each site, one HSN at each site, one TB nurse at each site, two follow-up research assistants, and two data entry personnel. Training was conducted by a team consisting of the principal investigator, a behavioral scientist, a Durban-based social worker, and the head of the Data Coordinating Center, and included lectures, question/answer, information-sharing, interactive problem solving and role plays. Some training was common to all study staff. TB nurses received training in universal precautions and safe handling of sputum specimens. The HSNs, experienced counselors with more advanced education, received training in strengths-based case management
[19]. HSNs were provided with standardized definitions of patient barriers (for example, competing needs, transportation, fear) and strengths (for example, self-efficacy, familial emotional support, spirituality) assessed at each patient contact. In addition, HSNs were given scripts and probes to prepare for their encounters with patients. The staff also received training in the ethical conduct of research and confidential handling of data from the principal investigator and the NIH online course on the protection of human research participants
[22].

### Follow-up process

Outcomes regarding successful linkage to each step on the HIV and TB care path are ascertained through review of medical records and registers at the study sites. In addition, external sources are used, including TB outcomes from the Department of Health as well as deaths as ascertained through the South African death registry. Finally, all participants, regardless of study arm, are contacted by telephone for a follow-up questionnaire, with a minimum of 3 call attempts starting at 9 months and finishing 12 months post-enrollment. The purpose of the 9 month follow-up questionnaire is to ascertain information regarding HIV care obtained outside of the study sites, as well as changes in family composition, emotional health, social support, and barriers to care compared to enrollment.

### Outcome measures

#### Primary outcomes

The primary outcome of the study is linkage to and retention in care assessed 9 months after enrollment for those HIV-infected individuals eligible for ART or TB treatment. The primary outcome is defined as: 1) 3 months on ART for ART-eligible HIV-infected patients, and 2) 6 months of TB treatment or 3 months on ART for HIV-infected patients co-infected with TB. Thus, for co-infected patients, a patient who links to either HIV or TB treatment is considered to have successfully reached the primary outcome. In the primary analysis, we will use data obtained from medical record review and TB treatment outcomes as documented by the Department of Health to minimize ascertainment bias in the navigator arm. HIV care received outside of the study sites will be assessed through self-report and will be used in sensitivity analyses.

#### Secondary outcomes

HIV-infected participants who are not eligible for ART or TB treatment at baseline cannot reach a primary outcome, but may reach a secondary outcome. We will examine mortality at 9 months, receipt of CD4 count results, receipt of TB laboratory results, attending ART literacy training for eligible participants, and repeat CD4 count for ART-ineligible participants at 6 months after enrollment as secondary outcomes. We hypothesize that people in the intervention group will be more likely to undergo CD4 count testing and retrieve their CD4 count and TB results.

Secondary outcomes will be derived from data collected via medical record review and participant 9-month follow-up interviews. Family members who answer a deceased subject’s telephone will be queried regarding date and cause of death, if known. A list of reported deaths and all unreachable patients will be cross-referenced with the South African death registry using South African identification numbers. Participants will be considered lost to follow-up if they or their family were unreachable by the study staff and do not appear in the national death registry.

### Sample size

Based on our prior work at McCord and St. Mary’s Hospitals, we estimated the HIV prevalence to be 35% among enrollees, with approximately 20% of HIV-infected enrollees co-infected with TB
[23-25]. Based on the ART-eligibility criteria at the start of the study, we anticipated that 22% of enrolled participants would be eligible to meet a primary outcome. Based on our prior work, we expected 35% of HIV infected/TB negative patients in the control group to achieve the primary outcome. Our power considerations were based on the assumption that the intervention will affect HIV and TB treatment outcomes similarly, which we thought reasonable given the lack of data on linkage to care interventions that distinguish between these groups. The study was originally powered (90%) to detect a 27% increase in linkage to care in the intervention arm. We planned to enroll 4,745 participants in total, with 1,661 HIV-infected individuals eligible to reach the study outcome.

In June 2012, the McCord Hospital HIV clinic closed due to the conclusion of PEPfAR funding, thus we ceased enrollment at the McCord outpatient department because participants could no longer meet the primary outcome at the enrollment site. We redeployed the McCord team to Mariannridge Clinic beginning in August 2012. Additionally, with the approval of the trial DSMB, we used actual trial data on HIV prevalence and the proportion who receive a CD4 count to refine our sample size requirements. The updated sample size called for an additional 149 patients, for a new total of 4,894 participants, 1,714 of whom are HIV-infected.

### Data collection

For HIV-related outcomes, the following data elements are collected: dates and results of HIV test, CD4 count and viral loads if available, dates of ART training, and ART initiation. Data are obtained from electronic and paper records, as well as patients’ self-report (Table 
2). Data on mortality will be obtained from clinical records, follow-up telephone contacts, and the national death registry.

**Table 2 T2:** List of study instruments, data elements and source of information

**Data collection instruments**	**Time of ascertainment**	**Data collected**	**Source**
Pre-screen checkpoints	Day of enrollment	Basic demographic information and eligibility assessment	Subject self report
Screening and baseline questionnaire	Day of enrollment	Demographic information, emotional health, social support, barriers and competing needs to care	Subject self-report
Contact information	Day of enrollment	Contact information to reach subject, including preferred language for SMS	Subject self-report
TB nurse questionnaire	Day of enrollment	TB symptoms and TB treatment history	Subject self-report
Health system navigator contact log	Day of enrollment and throughout	Perceived barriers to care and strengths to overcome barriers, time spent contacting participants	Medical record, subject self-report
Participant log	Day of enrollment and throughout	HIV test and CD4 results and retrieval, ART initiation, TB treatment dates and outcomes, date last seen	Medical record, death registry, subject self-report
9-month follow-up form	Patient telephone interview 9-mo after enrollment	HIV and TB care, demographic and clinical updates, emotional health, social support, and competing needs	Subject self-report
Study completion form	At 9-mo follow-up	Study endpoint (death, loss to follow-up, completed follow-up)	Medical record, HSN log, death registry

TB: Tuberculosis; HSN: Health system navigator.

For TB outcomes, the site of TB treatment, date of TB treatment initiation, date of TB treatment completion, date of assigned treatment outcome, and treatment outcome (cured, treatment completed, treatment defaulted, treatment failure, death) will be collected from study site TB registers as well as from the Department of Health’s TB outcomes database.

Information on research personnel resource utilization will be collected, such as the HSN time spent in face-to face contact with patients, sending SMS, and telephoning participants. This will be used to inform an anticipated cost-effectiveness analysis. Table 
2 provides a complete list of data collection tools.

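### Mortality and the care-step secondary outcomes are open to arm-dependent ascertainment that the plan guards against only for the primary outcome

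*Protocol article*

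**What the plan says.** The Primary outcomes section of the protocol article limits the primary analysis to record review and Department of Health TB outcomes, and gives the reason: "to minimize ascertainment bias in the navigator arm". Self-reported HIV care outside the study sites is kept for sensitivity analyses.

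The Secondary outcomes section draws no such line: "Secondary outcomes will be derived from data collected via medical record review and participant 9-month follow-up interviews". These outcomes are 9-month mortality, receipt of CD4 and TB results, ART literacy training, and a repeat CD4 count.

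The Data collection section gives the sources for death in two places. The text says: "Data on mortality will be obtained from clinical records, follow-up telephone contacts, and the national death registry". For the study completion form (death, loss to follow-up, completion), Table 2 says: "Medical record, HSN log, death registry". Table 2 also describes a participant log, kept from the day of enrollment onward. It holds CD4 results and their retrieval, ART initiation and date last seen, and self-report is one of its sources.

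Contact differs between the arms by design. In the navigator arm, "During each telephone contact, the HSN assessed where participants are on the HIV and TB care pathway", with calls scheduled from week 1 to week 16. A note to Table 1 adds that the navigator calls alternative contacts "if the subject is still unreachable". For the other arm, the Usual care section says: "The participants in the usual care arm had no further contact with the study staff until the 9-month follow-up phone call".

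**The concern.** The plan names a bias, more complete ascertainment in the navigator arm, and then protects one outcome from it. A log that only navigators keep has no usual-care counterpart. If it can establish a death or a vital status, one arm has an extra route to that finding. Likewise, if a participant tells a navigator in week 4 that she collected her CD4 result and this enters the participant log, nobody was scheduled to ask the same of a usual-care participant at that time.

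The two effects run in opposite directions. Extra deaths found in the navigator arm count against the intervention. Extra care steps recorded there count in its favour, on CD4 and TB result retrieval, which the plan expects to improve. The limitations paragraph of the Discussion accepts that self-report brings reporting bias, but answers it only for the primary analysis.

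**Working it through.** The documents state no figure for this bias, so there is none to reproduce. The check compares sources by arm and then illustrates size on assumed inputs.

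**1. Sources by arm**

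| Source | Navigator arm | Usual care arm |
|---|---|---|
| Clinic records and registers (Follow-up process) | yes | yes |
| 9-month call, at least 3 attempts (Follow-up process) | yes | yes |
| Registry check of reported deaths and all unreachable patients (Secondary outcomes) | yes | yes |
| HSN log (Table 2, study completion form) | yes | none exists |
| Self-report between enrollment day and month 9 (Table 2, participant log) | scheduled calls, weeks 1 to 16 | no study contact |

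The last two rows are the asymmetric ones. The HSN log row also conflicts with the mortality text, which omits that log. The phrase there about telephone contacts most naturally means the 9-month call. If it was meant to include navigator calls, the text itself would rely on a one-arm source.

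**2. How far the registry closes the gap for deaths**

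A usual-care participant whose death nobody reports is unreachable at month 9, and being unreachable triggers the registry check. What can still differ by arm is mainly a death that the clinic records and the family call miss and that cannot be matched by identification number, but that a navigator heard of.

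**3. Illustration of size, with no true effect**

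- Participants: 1,899 HIV-infected (Enrollment). The allocation ratio is not stated; 1:1 is assumed, so 1,899 / 2 ≈ 949 per arm.
- True rates and capture rates are assumed.
- Observed rate = true rate × capture, and d is the difference in observed rates.
- SE = √[p₁(1−p₁)/n + p₂(1−p₂)/n].
- False-positive rate = Φ(d/SE − 1.96) + Φ(−d/SE − 1.96).

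Worked case: true rate 50%, capture 90% versus 95%. Then p₁ = 0.450, p₂ = 0.475, d = 0.025 and SE = √(0.2475/949 + 0.2494/949) = 0.0229, so d/SE = 1.09. The false-positive rate is 0.193 + 0.001 = 0.194.

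| True rate | Capture, usual care vs navigator | Spurious difference | False-positive rate |
|---|---|---|---|
| 10% (mortality) | 90% vs 95% | 0.5 points | 7% |
| 10% (mortality) | 90% vs 100% | 1.0 point | 12% |
| 50% (care step) | 90% vs 95% | 2.5 points | 19% |
| 50% (care step) | 90% vs 100% | 5.0 points | 59% |
| 70% (care step) | 90% vs 95% | 3.5 points | 36% |
| 70% (care step) | 90% vs 100% | 7.0 points | 90% |
| any of these | 90% vs 90% | 0 | 5% |

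Outcomes confined to a subgroup, such as repeat CD4 count in ART-ineligible participants, have fewer than 949 per arm. Their false-positive rates would be lower for the same spurious difference.

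**4. The common 9-month call**

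Suppose 60% truly received a CD4 result in each arm, records hold 45 points of that, and the call reaches 80% of the navigator arm and 70% of usual care. Then 45 + 15 × 0.80 = 57.0% and 45 + 15 × 0.70 = 55.5%. The spurious difference is 1.5 points and the false-positive rate about 10%. Pooled reach so far is higher than assumed here. From Follow-up, 1,329 / (1,899 − 114 − 52 − 252) = 1,329 / 1,481 ≈ 90%, taking the reported categories as non-overlapping. No figure by arm is given.

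**The case against.** A reader might infer that navigator logs feed the care-step outcomes. The documents do not say so. Table 2 lists the HSN log as a source only for the study completion form, and the log's own content is barriers, strengths and contact time. That self-report in the participant log comes partly from navigator calls is an inference from its timing.

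A reader might also infer that the 9-month interview is biased by arm. Its procedure is the same in both arms, and every enrollee gave an alternative contact. Better reach after four months of navigator contact is plausible but undocumented.

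Nor do the documents support a claim of a material false mortality excess. The registry check covers both arms, and scheduled navigator calls end at week 16. Loss to follow-up is a completion status, not a listed secondary outcome, and no comparison of it between arms is planned.

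The ranking of sources is ordinary content for an analysis plan that is not shown. That is fair as far as it goes, but the conflict between Table 2 and the mortality text, and the safeguard stated for one outcome only, are in the article itself.

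The strongest objection concerns the remedy. Navigators handed out lists of other facilities, and the Discussion says that off-site care became a greater problem when the McCord enrollment site closed. A record-only analysis may therefore miss more completed steps in the navigator arm. This stands, and it rules out treating record-only as the one unbiased answer.

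**Conclusion.** The secondary comparisons are open to arm-dependent ascertainment; the documents do not show that they are biased. Three things are established. Table 2 admits a one-arm source for death and loss status, against the mortality text. The participant log accepts self-report over a period when only one arm has scheduled study calls. The safeguard adopted for the primary outcome has no counterpart for the secondary outcomes.

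The distortion of mortality is probably small because of the registry check. For self-reported care steps it could be larger, but its size is unknown. Every magnitude above rests on assumed true rates, assumed capture and 1:1 allocation.

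One further route is conditional. The analysis plan counts participants who cannot be found and have no record data as not linked, and secondary outcomes are to be analyzed similarly. If that rule carries over, unequal reach would turn directly into an apparent difference. The primary outcome is not affected by this point.

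**What to change.** - Reconcile Table 2 with the text on mortality sources, and state whether the HSN log may determine death or loss to follow-up.
- Base between-arm comparisons on sources available in both arms: clinic records and registers, the common 9-month call, and a death-registry match of all HIV-infected participants with an identification number, not only those reported dead or unreachable.
- Use deaths or care steps known only from navigator contacts in sensitivity analyses.
- Flag the source of each outcome and report the sources by arm.
- Show each care-step outcome twice, from records only and with 9-month self-report added. State that the record-only version may undercount off-site care, possibly more in the navigator arm.

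The cost is analysis-plan wording, a source flag in the data, and the extension of a registry match already planned for part of the cohort. The article reports that ascertainment is still under way and blinded to outcomes across arms, so the sources can be settled without knowledge of the results.
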